# Addition of Propranolol in Resistant Arterial hypertension Treatment (APROPRIATE study): study protocol for a randomized double-blind placebo-controlled trial

**DOI:** 10.1186/s13063-017-1863-1

**Published:** 2017-03-14

**Keywords:** Propranolol, Resistant hypertension, Randomized controlled trial, Sri Lanka

## Abstract

**Background:**

Resistant hypertension is defined as an uncontrolled blood pressure despite treatment at best-tolerated doses with at least three antihypertensive agents including a diuretic. It is an emerging public health problem. At present clinical trial data on management of resistant hypertension is limited. Management is largely based on observational studies and expert opinions. Propranolol is a nonselective beta blocker. Several studies have confirmed that propranolol has a significant hypotensive action, both when used alone and as an adjuvant therapy. At present there are no prospective, randomized, clinical studies evaluating the effectiveness of propranolol in patients with resistant hypertension. Therefore, we have designed a prospective randomized trial to evaluate the safety and efficacy of propranolol in patients with resistant hypertension.

**Methods/design:**

The study will be conducted as a randomized, double-blind, placebo-controlled clinical trial for a period of 3 months. The study has been approved by the Ethics Review Committee of the Faculty of Medicine, University of Colombo. A total of 200 adults with resistant hypertension will be recruited for the study. They will be randomly assigned to the test and placebo groups on a 1:1 ratio. The test group will receive propranolol 40 mg three times a day and the control group will receive an identical placebo capsule. The study drugs will be double blinded to both investigators and subjects. The visits and the evaluations will be done as follows: screening (visit 0), 1 month (visit 1), 2 months (visit 2) and 3 months (visit 3). The primary outcomes of the study is to find a statistically significant difference between the fall in mean systolic and mean diastolic blood pressure measured by ABPM (ambulatory blood pressure monitoring) from baseline between the two groups. Data will be analyzed using SPSS v16.

**Discussion:**

To our knowledge this is one of the first randomized controlled trials evaluating the effects of propranolol in resistant hypertension. This study will provide the necessary groundwork for future large-scale, multicentered clinical trials. The result, positive or negative, should provide a step change in the evidence guiding current and future policies regarding treatment of resistant hypertension.

**Trial registration:**

Sri Lanka Clinical Trials Registry, identifier: SLCTR/2016/002. Registered on 27 January 2016; Study protocol version 2.1.

**Electronic supplementary material:**

The online version of this article (doi:10.1186/s13063-017-1863-1) contains supplementary material, which is available to authorized users.

## Background

Resistant hypertension is defined as an uncontrolled blood pressure despite treatment (>140/90 mmHg or >150/90 mmHg in patients over the age of 60 years) with at least three antihypertensive agents at best-tolerated doses, including a diuretic [1, 2]. It is an emerging public health problem, associated with substantial morbidity and mortality [3, 4]. Studies indicate that the prevalence of resistant hypertension is 10–20% in the general hypertensive population [5, 6].

At present clinical trial data on management of resistant hypertension is limited. Management is largely based on observational studies and expert opinions. Recent studies support the use of spironolactone as the “first-line” fourth drug for treating resistant hypertension [7, 8]. However, to date there have been no randomized clinical trials comparing the effectiveness of various drug combinations in the treatment of resistant hypertension [9]. Though sympathetic denervation showed some promise in the treatment of resistant hypertension from the initial studies, subsequent studies failed to show a sustained long-term reduction of blood pressure [10].

Propranolol is a nonselective beta blocker. Several studies have confirmed that propranolol has a significant hypotensive action, both when used alone and as an adjuvant therapy [11]. However, the exact mechanism of the antihypertensive effect of propranolol is still poorly understood. It is possible that the hypotensive effect of propranolol is not only due to its peripheral beta-receptor blocking action [12]. Propranolol, with its high lipophilic tendency, achieves high concentrations in cerebrospinal fluid and blocks the central cardiac sympathetic outflow. Increased sympathetic nervous system activity has been documented in systole-diastolic hypertension and in isolated systolic hypertension [13]. Furthermore, sympathetic nervous system activity increases progressively and in parallel with stages of hypertension [14]. Central sympathetic outflow blockage may be important in reducing transient rises in blood pressure which occurs in response to various stimuli. In addition, propranolol is also known to act through the renin-angiotensin system to produce hypotension [15]. The role of stress as a risk factor for resistant hypertension also needs to be considered as drugs alone have not been very successful in controlling blood pressure in patients with resistant hypertension [16]. Propranolol is sometimes used as an anxiolytic in the premedication of surgical patients [17]. Hence, propranolol may be beneficial in reducing stress and anxiety in patients with resistant hypertension. At present there are no prospective, randomized, clinical studies evaluating the effectiveness of propranolol in patients with resistant hypertension. Therefore, we designed a prospective randomized trial to evaluate the efficacy and safety of propranolol in patients with this condition.

## Methods/design

### Objectives and hypothesis

Hypothesis: blood pressure in patients with resistant hypertension treated with propranolol will be lower than that of the control group.

Primary objective: the study aims to compare the safety and efficacy of propranolol in patients with resistant hypertension when added to a multidrug combination (at least three drugs) consisting of a diuretic and an angiotensin-converting enzyme inhibitor (ACEI)/angiotensin-II receptor blocker (ARB), a centrally acting drug, and an alpha blocker or calcium channel blocker.

Secondary objectives: (1) to describe the sociodemographic and clinical characteristics of patients with resistant hypertension at baseline, (2) to describe the complications and cardiovascular risk associations of patients with resistant hypertension at baseline, (c) to describe the impact of propranolol administration on serum/urinary electrolytes and oxidative stress in patients with resistant hypertension and (4) to assess sodium excretion in patients with resistant hypertension at baseline and following propranolol therapy.

### Study design

The study will be conducted as a randomized, double-blind, placebo-controlled clinical trial for a period of 3 months to assess the efficacy of using propranolol in the management of patients with resistant hypertension at the medical outpatient clinics of the National Hospital of Sri Lanka, Colombo, Sri Lanka. Figure 1 provides an overview of the study. This protocol was written following the Standard Protocol Items: Recommendations for Interventional trials (SPIRIT) Checklist (see Additional file 1). The schedule of trial enrollment, interventions and assessments is presented in Fig. 2.

**Fig. 1 Fig1:**
[figure not shown]
Study flow chart

**Fig. 2 Fig2:**
[figure not shown]
Schedule of enrollment, interventions and assessments (Standard Protocol Items: Recommendations for Interventional trials (SPIRIT) figure)

### Sample size

The sample size calculation was based on formulae for analysis between differences of means. The value for alpha was set at 0.05 and the value for 1 − beta was set at 0.9. Sample sizes were calculated for a difference of systolic blood pressure by 10 mmHg and diastolic blood pressure by 5 mmHg. Standard deviation values were taken as 18 mmHg for systolic blood pressure and 10.7 mmHg for diastolic blood pressure as per prior investigations on patients with resistant hypertension. Using the above parameters the calculated sample sizes were 140 and 180 patients to detect differences in systolic and diastolic blood pressures, respectively. Using the greater number and adjusting for dropout and noncompliance rates a sample of 200 patients will be recruited with a 1:1 allocation per group.

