### Outcomes

Primary outcomes: the primary outcomes of the study are to find a statistically significant difference between the fall in mean systolic and mean diastolic blood pressure measured by ABPM (ambulatory blood pressure monitoring) from baseline between the two groups.

Secondary outcomes:To determine the difference in cardiovascular outcomes, including acute coronary syndrome, acute stroke and acute heart failure, between groupsTo determine the variations in plasma and urinary electrolytes between the two groups at measured endpointsTo assess renal outcomes as measured by the glomerular filtration rate between groupsTo determine variations in plasma renin activity (PRA) and angiotensin:aldosterone ratios between the study groupsTo determine differences in oxidative stress between the study groups using nitric oxide as a surrogate markerTo assess safety outcomes, including the incidence of serious adverse effects, between the two groups at measured endpoints

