### Statistical analysis

Parametric and nonparametric statistical tests will be applied using the SPSS version 16 (SPSS Inc., Chicago, IL, USA) and Stata/SE 10.0 (StataCorp Inc., College Station, TX, USA) for data analysis. Descriptive data will be analyzed for linearity and will be expressed as percentages, median and mean. The two groups will be compared for uniformity on sociodemographic variables, clinical manifestations and laboratory parameters at baseline. After completion, primary and secondary outcomes will be compared in the groups using statistical methods for comparison of means and using regression analysis. For each of the outcomes, multilevel regression analysis will be used to examine differences between trial arms. For binary outcomes the model will be logistic and for continuous outcomes the model will be linear regression. All analyses will follow intention-to-treat principles and a prespecified analysis plan. Where appropriate, sensitivity analyses will be conducted (for example, control for additional covariates; and bootstrapped *p* values for skewed outcomes). In the case of missing data values, we will apply mean imputation and regression imputation where rates are low, and consider multiple imputations where they exceed 10%. A *p* value < 0.05 will be considered significant.

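### The diastolic sample size of 180 gives about 88% power, not 90%, on its own inputs, and the SDs are not tied to the primary outcome, the fall in ambulatory pressure

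*Protocol article*

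**What the plan says.** The Sample size section describes a two-group comparison: "The sample size calculation was based on formulae for analysis between differences of means". It sets alpha at 0.05 and power at 0.9. The effects are given as follows: "Sample sizes were calculated for a difference of systolic blood pressure by 10 mmHg and diastolic blood pressure by 5 mmHg". For variability it says "Standard deviation values were taken as 18 mmHg for systolic blood pressure and 10.7 mmHg for diastolic blood pressure", and gives the source only as "as per prior investigations on patients with resistant hypertension". The resulting totals are 140 for systolic and 180 for diastolic pressure. The larger is raised to 200 to allow for dropout and noncompliance, with equal allocation.

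The Outcomes section defines the primary outcome as a between-group difference in "the fall in mean systolic and mean diastolic blood pressure measured by ABPM (ambulatory blood pressure monitoring) from baseline". The Statistical analysis section plans comparisons of means and multilevel regression, linear for continuous outcomes. It does not say whether the baseline value enters the model.

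**The concern.** Two things need attention in the diastolic calculation, which sets the size of the trial.

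First, the stated inputs do not give the stated answer. This needs no outside assumption about correlation.

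Second, the text never connects its SDs to the variable being tested. An SD of a single reading and an SD of a change are different quantities, related through the correlation between baseline and follow-up. If the SDs are of single readings and the falls are compared without adjustment, a low correlation makes the real power lower than the reader is told. Likewise, an SD of office pressure need not equal one of an ambulatory mean. The reader cannot judge the 90% claim without knowing which SD was used.

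**Working it through.** **Inputs.** From the Sample size section: differences 10 and 5 mmHg, SDs 18 and 10.7 mmHg, alpha 0.05, power 0.90, 1:1 allocation, totals 140 and 180. Assumed: a two-sided test (the article does not state sidedness), equal SDs at baseline and month 3, and the correlation r.

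**Step 1: reproduce the stated totals.** Per arm, n = 2(1.960 + 1.282)² SD²/d² = 2 × 10.507 × SD²/d².

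- Systolic: 2 × 10.507 × 324/100 = 68.1, so 69 per arm and 138 in total. The t-test version gives 140. The stated 140 is reproduced.
- Diastolic: 2 × 10.507 × 114.49/25 = 96.2, so 97 per arm and 194 in total. The t-test version gives 196. The stated 180 is not reproduced.

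Other settings do not give 180 for diastolic pressure either. A one-sided 0.05 gives 158; two-sided with power 0.80, 0.85 or 0.95 gives 144, 166 or 240. An SD of about 10.35 would be needed.

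**Step 2: diastolic power with 180 evaluable.** The standard error is 10.7 × √(2/90) = 1.595. Then 5/1.595 − 1.960 = 1.175, and Φ(1.175) = 88.0% (87.7% by the t-test). With all 200 evaluable it is 91.1%.

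**Step 3: if the SDs are of levels.** The SD of a fall is SD × √(2(1 − r)). The residual SD of the month-3 value adjusted for baseline is SD × √(1 − r²). For example, at r = 0.3 the SD of a diastolic fall is 10.7 × √1.4 = 12.66, the standard error is 12.66 × √(2/90) = 1.887, and Φ(5/1.887 − 1.960) = Φ(0.689) = 75.5%.

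Diastolic power, 90 per arm:

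| r (assumed) | SD of fall | Power, falls (normal) | Power, falls (t) | Adjusted SD | Power, adjusted (normal) |
|---|---|---|---|---|---|
| 0 | 15.13 | 60.1% | 60% | 10.70 | 88.0% |
| 0.2 | 13.53 | 69.8% | 69% | 10.48 | 89.2% |
| 0.3 | 12.66 | 75.5% | 75% | 10.21 | 90.8% |
| 0.4 | 11.72 | 81.6% | 81% | 9.81 | 92.8% |
| 0.5 | 10.70 | 88.0% | 88% | 9.27 | 95.2% |
| 0.6 | 9.57 | 93.9% | 94% | 8.56 | 97.5% |
| 0.7 | 8.29 | 98.2% | 98% | 7.64 | 99.2% |

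Systolic power for falls (normal, 90 per arm) is 83.8%, 88.3%, 92.5% and 96.1% at r = 0.2, 0.3, 0.4 and 0.5.

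**Step 4: where 90% is reached with 180 evaluable.** The largest SD that gives 90% is d/(3.2415 × √(2/90)), which is 10.35 for diastolic and 20.69 for systolic pressure.

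- Falls, diastolic: r = 1 − (10.35/10.7)²/2 = 0.53 (0.54 by the t-test).
- Falls, systolic: r = 1 − (20.69/18)²/2 = 0.34.
- Adjusted, diastolic: r = √(1 − (10.35/10.7)²) = about 0.25.

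**Step 5: adjusted against unadjusted.** The ratio of the two SDs is √(1 − r²)/√(2(1 − r)) = √((1 + r)/2), which is at most 1. Adjustment is therefore never worse than comparing falls, apart from one degree of freedom.

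**The case against.** A reader might infer that the calculation uses the wrong SD. The article does not support that. It uses blood pressure loosely for the effect as well as for the SD, and the source is not described, so 18 and 10.7 could already be SDs of change. In that case step 3 falls away, and only the arithmetic shortfall and the office or ambulatory question remain.

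A reader might also infer that the stated power holds only at a single correlation. That is not so. At r = 0.5 the SDs of level and of change coincide, and any higher r gives more power. At r = 0.5 itself, diastolic power with 180 is 88% rather than 90%.

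The low figures need a low correlation, and nothing in the article points to one. They also need an unadjusted comparison of falls. The article plans regression for every outcome under a prespecified plan that is not shown, and a baseline covariate may be specified there. Its absence from the article is therefore not a fault. If baseline is adjusted for, an SD of level is conservative at every positive r.

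All of this stands, and it makes the correlation argument conditional. It does not touch the diastolic arithmetic, nor the fact that the Sample size section leaves its SDs unidentified.

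**Conclusion.** The diastolic total is too small for its own stated inputs: 194 to 196 are needed for 90% power against 180 given, and 180 evaluable patients give about 88%. This rests only on the article's figures and a two-sided test, the reading that reproduces the systolic 140. The shortfall in power is small, but it falls on the comparison that fixes the trial's size.

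The SDs are unidentified rather than shown to be wrong. If they are SDs of level, equal at both times, diastolic power for unadjusted falls with 180 evaluable is below 90% for r under about 0.54 and above it for higher r; the systolic threshold is about 0.34. The values of r are assumptions. Any effect of using office rather than ambulatory SDs cannot be sized from the article.

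**What to change.** In the Sample size section, state whether 18 and 10.7 are SDs of level or of change, and of office or ambulatory pressure. Correct the diastolic figure: either 194 to 196 patients for 90% power, or about 88% power with 180 evaluable.

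Make the primary analysis the month-3 ambulatory mean in a linear model with the baseline ambulatory mean as covariate, and restate the power for that analysis with the assumed r and its basis.

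The cost is wording. Baseline ambulatory monitoring is already scheduled at the enrollment visit, and the Trial status section says enrollment has not begun. No more patients are requested. The downside is that the stated power may become slightly less favourable: if r is below about 0.25, adjusted diastolic power with 180 evaluable still lies between 88% and 90%. It would also need restating if the SDs prove to be office values.

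### The diastolic sample size of 180 does not follow from its stated inputs, which give 194 to 196; either the number or the standard deviation needs correcting

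*Protocol article*

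**What the plan says.** The Sample size section of the protocol article describes a comparison of two means with 1:1 allocation. On the error rates it states "The value for alpha was set at 0.05" and power (one minus beta) of 0.9. On the effects: "Sample sizes were calculated for a difference of systolic blood pressure by 10 mmHg and diastolic blood pressure by 5 mmHg". On variability: "Standard deviation values were taken as 18 mmHg for systolic blood pressure and 10.7 mmHg for diastolic blood pressure", attributed to earlier work in resistant hypertension. From these inputs it reports that "the calculated sample sizes were 140 and 180 patients to detect differences in systolic and diastolic blood pressures, respectively". It continues: "Using the greater number and adjusting for dropout and noncompliance rates a sample of 200 patients will be recruited".

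Neither the sidedness of the test nor the rate of dropout or noncompliance is given. The Statistical analysis section adds only that a p "value < 0.05 will be considered significant". Under Outcomes, the falls in mean systolic and in mean diastolic ambulatory pressure are both primary.

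**The concern.** The section lists every input that a two-group comparison of means needs, apart from sidedness, and presents 140 and 180 as the result. The systolic figure can be reproduced; the diastolic figure cannot. The diastolic calculation is the larger of the two and so determines how many patients are recruited. If 180 is too small for its inputs, the margin between 180 and 200 is partly used up before any patient is lost. The trial could then not claim both 90% diastolic power and the allowance for losses that this margin appears to represent.

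**Working it through.** **Inputs** (Sample size section): alpha 0.05; power 0.90; differences 10 mmHg systolic and 5 mmHg diastolic; SDs 18 and 10.7 mmHg; 1:1 allocation. Two-sided testing is an assumption, tested in step 3.

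**Formula** (normal approximation, per arm):

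n = 2 × (1.960 + 1.282)² × SD² / difference²

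**1. Systolic, to reproduce the stated 140.** 2 × 10.507 × 18² / 10² = 68.09, so 69 per arm and 138 in total. The t-test needs 69.06, so 70 per arm and 140 in total. The stated 140 is reproduced, exactly by the t-test and within 2 patients by the normal formula.

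**2. Diastolic, same method.** 2 × 10.507 × 10.7² / 5² = 96.24, so 97 per arm and 194 in total. The t-test needs 97.21, so 98 per arm and 196 in total. The stated 180 is 14 to 16 patients short (14/194 = 7%; 16/196 = 8%).

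**3. Could another method give 180?** Totals by normal formula / t-test:

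| Variant | Systolic (stated 140) | Diastolic (stated 180) |
|---|---|---|
| Two-sided, power 0.90 | 138 / 140 | 194 / 196 |
| One-sided, power 0.90 | 112 / 114 | 158 / 160 |
| Two-sided, power 0.85 | 118 / 120 | 166 / 168 |
| Two-sided, power 0.80 | 102 / 104 | 144 / 146 |
| Two-sided, alpha 0.025, power 0.90 (normal only) | 162 | 228 |

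Rounding the constant to 10.5 gives 4 × 10.7² × 10.5 / 25 = 192.3. No variant gives 180, and only the first row fits the systolic figure.

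**4. Could another input give 180?** Solving the normal formula for 90 per arm gives SD = 5 × √(90/2) / 3.2415 = 10.35. With the rounded value 10.3 the totals are 180 (normal) and 182 (t-test). Alternatively, with SD 10.7 the difference would have to be 10.7 × √(2/90) × 3.2415 = 5.17 mmHg.

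**5. Power with 200 recruits if SD 10.7 is right.** Normal approximation: power = Φ(difference / (SD × √(2/n)) − 1.960). At 90 per arm this is Φ(5/1.595 − 1.960) = Φ(1.175) = 88.0%. The loss rates below are assumptions:

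| Loss | Evaluable | Diastolic power, normal | t-test |
|---|---|---|---|
| 0% | 200 | 91.1% | 90.8% |
| 2% | 196 | 90.5% | 90.2% |
| 3% | 194 | 90.2% | 89.9% |
| 5% | 190 | 89.6% | 89.3% |
| 10% | 180 | 88.0% | 87.7% |
| 15% | 170 | 86.1% | 85.8% |
| 20% | 160 | 84.0% | 83.6% |

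The 10% row is the one implied by the text, since 1 − 180/200 = 10%. Systolic power at 180 evaluable is 96.1% (normal) or 96.0% (t-test).

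**6. Recruits needed to hold 90% diastolic power at 10% loss.** 194/0.90 = 215.6, so 216; 196/0.90 = 217.8, so 218.

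**The case against.** The strongest reply is that the wrong number may be the SD and not the 180. The SD comes from earlier studies that cannot be checked from this document, and a value of about 10.3 would make 180 and 90% power correct. This stands. It means that the section contradicts itself, without showing which entry is at fault, and an instruction simply to replace 180 could introduce an error.

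A second reply is that the effect is small. This also stands: at 10% loss the shortfall from 90% is 2.0 points (normal) or 2.3 points (t-test), 200 evaluable patients still exceed the target, and systolic power is ample.

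A third is that an article may leave detail to the full protocol. That excuses the missing loss rate, but not a stated result that its stated inputs do not produce.

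Two stronger readings are tempting and should not be drawn:

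- **That the trial falls below 90% power after its planned losses.** No loss rate is stated. The 10% is only worked back from 180 and 200.
- **That noncompliance was wrongly handled as lost patients.** A reader might infer this because the number is adjusted for noncompliance while "All analyses will follow intention-to-treat principles", so that noncompliant patients would stay in the analysis and dilute the difference. But the section does not say how the adjustment was made, and raising the sample size is also the usual way to offset dilution. For example, 180/0.95² = 199.4, so 200 fits a 5% dilution allowance as well as it fits 180/0.90. Power figures for particular noncompliance rates would rest on rates that the document does not give.

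**Conclusion.** The statement is wrong as written: under the stated inputs the diastolic requirement is 194 to 196, not 180, and the total of 200 is built on that figure. The only added assumption is two-sided testing, which the section's own systolic number supports.

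What this means for power depends on the SD. If 10.7 mmHg is right, 90% diastolic power holds only with losses up to about 2% (t-test) or 3% (normal), and is about 88% if 10% are lost. If the SD is a misprint for about 10.3, the 180 and the 90% stand and only the printed input is wrong. Either way the point should be fixed. It does not undermine the design, because the shortfall is about 2 points under the inferred loss.

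**What to change.** Keep 200 patients. Check the diastolic SD against the source from which it was taken.

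- **If 10.7 mmHg is right:** replace 180 with 194 (normal formula) or 196 (t-test), naming the method; state the loss rate assumed; and restate the diastolic power as about 88% at 10% loss, alongside about 96% for systolic pressure at 180 evaluable.
- **If the SD is a misprint:** correct the SD, leave 180 in place, and state the loss rate assumed.

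In both cases, say that the calculation is two-sided.

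The cost is a change of wording in one section and, in the first case, a slightly less favourable stated power. No extra patients are needed. The Trial status section says that enrollment has not begun, so the correction can be made before recruitment.
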